#### Treatment Data

The following data regarding treatment will be obtained:

• Administration of the first and second study drug doses; with details regarding timing and amount per dose;

• Hydration scheme before angiographic procedure: type of solution, total volume and duration of infusion;

• Angiographic procedure: date, hour and type (coronary or peripheral; diagnostic or therapeutic; if therapeutic, angioplasty, bare metal stent, drug-eluted stent or a combination of them;

• Contrast: type, volume administered;

• Whether the procedure was indicated for a patient with acute coronary syndrome.

#### Short-Term Follow-up Data

This is the main follow-up visit. Patients will have a serum creatinine measured between 48 and 96 hours after angiography for evaluation of the study primary outcome. Other data elements which will be recorded are:

• Administration of the third and fourth study drug doses; with details regarding timing and amount per dose;

• Hydration scheme after angiographic procedure: type of solution, total volume and duration of infusion;

• Whether the patient undergone an angiographic procedure within 72 hours after the index angiography; if yes, date, type, and measures to prevent CIN;

• Vital status; in case of deaths, date and cause;

• Need of dialysis.

#### One month follow-up data

Research personnel will contact patients 30 days after the angiographic procedure and record the occurrence of:

• Angiographic procedure: date, type, measures to prevent CIN;

• Vital status; in case of deaths, date and cause;

• Need of dialysis.

#### Adverse events form

This form contains questions for adverse events which may occasionally occur after acetylcysteine (nausea, emesis, urticaria, bronchospasm), open questions for registration of any other adverse event, and a question for severe adverse event with a field for detailing the event.

#### Clinical Data Management System (CDMS) and Quality Control

The ACT study CDMS is a web based system that has been developed on a Microsoft SQL^® ^platform by a team of programmers of the Research Institute – HCor. Its functionalities include: patient registration, 24-hour concealed randomization, data entry, data cleaning and exportation for analysis.

The CDMS also provides reports on the status of the study forms (completed forms, overdue forms), weekly study recruitment by center and graphs of observed and expected cumulative recruitment.

### Sample size

Based on a recent systematic review and meta-analysis of 26 randomized controlled trials, we anticipate an incidence of CIN at 48 to 96 hours of approximately 15%[16] In order to detect a 30% relative risk reduction (RRR), with 90% statistical power, and a two-tailed alpha of 5%, we will need to include at least 2,300 patients.

### Statistical Analysis Plan

All analysis will follow the intention-to-treat principle. The effect of acetylcysteine versus placebo on the primary endpoint, incidence of CIN between 48 to 96 hours, will be evaluated with a chi-square test. The magnitude of association will be presented as a risk ratio, with 95% confidence interval and number needed to treat (NNT). Statistical significance will be inferred using a significance level of 0.05.

Secondary outcomes evaluated 30 days after randomization will be presented as Kaplan-Meier curves according to the assigned treatment, and tested with the log-rank method. Hazard ratios and 95% confidence intervals will be calculated using non-adjusted Cox proportional hazards.

The incidence of the primary outcome will be analyzed in pre-specified subgroups using risk ratios and 95% confidence intervals. A subgroup effect will be inferred when the chi-squared test for homogeneity of effects is statistically significant. The following subgroups will be analyzed: 1) ≤70 year-old versus >70 year-old; 2) Male vs. female; 3) No previous renal failure vs. previous renal failure (serum creatinine >1.5 mg/dL); 4) Not diabetic vs diabetic; 5) Amount of contrast agent <140 mL vs. ≥140 mL. [17]

In the main trial publication, we also plan to include a random effects (DerSimonian-Laird) meta-analysis to combine ACT's results with those of previous randomized controlled trials evaluating acetylcysteine versus placebo for prevention of contrast-induced nephropathy. [18]

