### Randomization and Allocation Concealment

Patients are randomized after providing a written informed consent in a 1:1 ratio to receive acetylcysteine or matching placebo. The random allocation list was generated in random permuted blocks of variable size (4, 6, 8 or 10) and was stratified by investigator centre. In order to guarantee concealment of the allocation list, randomization is implemented through a 24-hour web-based automated randomization system, making the sequence allocation totally unpredictable for the professionals responsible for entering the patients in the trial in each centre. The randomization list was generated and implemented by the The ACT study Clinical Data Management System (CDMS), a web based system that has been developed on a Microsoft SQL^® ^platform by a team of programmers of the Research Institute – Hcor, Sao Paulo, Brazil.

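### The primary chi-square test ignores the centre stratification and the recorded risk factors: valid and adequately powered, but a small, free gain in efficiency is left unused

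*Protocol article*

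**What the plan says.** Protocol article, Randomization and Allocation Concealment: patients are allocated 1:1 and the list used "random permuted blocks of variable size (4, 6, 8 or 10) and was stratified by investigator centre". Trial Centers gives 54 centres, so about 2,300/54 = 43 patients per centre.

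Statistical Analysis Plan: the primary endpoint, "incidence of CIN between 48 to 96 hours, will be evaluated with a chi-square test", is reported as a risk ratio with 95% confidence interval and NNT. For the 30-day outcomes the curves are compared by log-rank, and "Hazard ratios and 95% confidence intervals will be calculated using non-adjusted Cox proportional hazards". Age, sex, creatinine above 1.5 mg/dL, diabetes and contrast volume appear as subgroup factors only.

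Eligibility names renal failure, diabetes, heart failure, shock and age over 70 as risk factors for CIN. Baseline Data records the eligibility criteria, date of birth and serum creatinine for each patient.

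Sample size: "In order to detect a 30% relative risk reduction (RRR), with 90% statistical power, and a two-tailed alpha of 5" per cent, "we will need to include at least 2,300 patients".

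**The concern.** Blocking within centre balances the arms on centre, so centre differences in CIN risk largely drop out of the treatment contrast. A crude test still counts them as random error. If centres differ, its standard error is somewhat too large and its p-value somewhat too high.

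Differences are plausible from the article itself. Cointerventions recommends hydration but lets volume and flow vary and leaves other management to the responsible doctor. Contrast type and volume are recorded, not fixed.

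The covariate part is separate. Subgroup analyses add no precision to the overall estimate, whereas adjusting for strong predictors would. At stake is a little precision in a trial sized right at its 90% target, obtainable at no cost in data.

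**Working it through.** **1. The plan's own figure.** Inputs from Sample size: 15% control risk, 30% relative reduction (hence 10.5%), 90% power, two-sided 5%, 1:1.

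- Unpooled: n per arm = (1.960 + 1.282)² × (0.15×0.85 + 0.105×0.895) / 0.045² = 1,149.2, rounded up to 1,150, or 2,300 in total.
- Pooled variance under the null: 1,153 per arm, 2,306 in total.
- Power of the crude test at 1,150 per arm: 89.9%.

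The stated size reproduces with the crude test, so planned test and sample size agree.

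**2. Ignoring centre.** The article gives no between-centre variation, so the SD of centre log-odds is an assumption: 0, 0.3, 0.5, 0.8. As a guide, around 15% (logit −1.735), ±1.96 SD spans about 6% to 32% at SD 0.5 and about 4% to 46% at SD 0.8. The top value is therefore a wide spread.

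Simulation: 54 unequal centres, 2,300 patients, blocks of 4, 6, 8 or 10, 1,500 trials per setting. The SE columns give the mean estimated SE of the log risk ratio.

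| Centre SD | Crude SE, no effect | MH SE, no effect | Ratio | Ratio at RR 0.70 | Power, crude / CMH |
|---|---|---|---|---|---|
| 0 | 0.0995 | 0.0996 | 1.001 | 1.001 | 89.9% / 89.7% |
| 0.3 | 0.0996 | 0.0991 | 0.996 | 0.997 | 90.7% / 90.7% |
| 0.5 | 0.0995 | 0.0981 | 0.985 | 0.989 | 89.4% / 89.4% |
| 0.8 | 0.0996 | 0.0959 | 0.963 | 0.971 | 91.2% / 92.3% |

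The largest overstatement is 1/0.963 = 1.038, about 4%. The implied type I error of the crude test is 2 × [1 − Φ(1.960/ratio)]: 4.7% at ratio 0.985 and 4.2% at 0.963. The simulated rejection rates themselves cannot settle this, since 1,500 runs carry a Monte Carlo error of √(0.05×0.95/1,500) = 0.6 points. A further simulation of the design gave 4.9%, 5.3%, 4.6% and 4.2% at the four SDs, which is consistent.

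The estimates hardly differ in actual spread: at SD 0.8 with no effect, the empirical SD is 0.0947 crude and 0.0944 stratified. Stratifying mainly makes the reported SE match the precision that blocking has already achieved.

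On the interval: at RR 0.70 the crude SE is √(0.895/(0.105×1,150) + 0.85/(0.15×1,150)) = 0.111, giving 0.563 to 0.870. A 3% smaller SE gives 0.567 to 0.865.

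**3. Covariates.** Prognostic strength is not given and is assumed. The SE factor is √(1 − R²). The crude design has 1.960 + 1.278 = 3.238 standard errors at 89.9% power, so adjusted power is Φ(3.238/factor − 1.960).

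| Assumed AUC | SE factor | Power |
|---|---|---|
| 0.58 | 0.995 | 90.2% |
| 0.64 | 0.986 | 90.7% |
| 0.71 | 0.964 | 91.9% |
| 0.75 | 0.945 | 92.9% |

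The gain is about 0.3 to 3 points.

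**4. Cox models.** Data Monitoring Committee expects 2% to 3% death or dialysis, that is 46 to 69 events in 2,300 patients. In simulation (300 trials per setting) with a prognostic covariate, the SE of the log hazard ratio was 0.337 to 0.338 unadjusted and adjusted at 2%. At 3% it was 0.273 to 0.276 unadjusted and 0.273 to 0.277 adjusted. There is no narrowing. Spread over 54 centres, this is 0.9 to 1.3 events per centre.

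**The case against.** The strongest reply is that nothing here is wrong. An unadjusted test after stratified randomization controls the type I error, the sample size was built on that test, and it delivers its power. Every gain above depends on inputs the article does not give, and the centre gain is zero if centres do not differ. The full analysis plan is not shown and may hold adjusted analyses. All of this stands, and it limits the point to a matter of efficiency. It does not remove the point, because the article does name the primary test, and that test does not follow the randomization. The stratified test also lost nothing material when centres did not differ.

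A reader might infer more, without support from the article:

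- That the primary interval is simply too wide. That is conditional on centre differences.
- That failing to attain exactly 5% is a defect. The departure is downward, so error is not inflated.
- That the unadjusted Cox intervals are too wide. Adjustment did not narrow them, and stratifying 46 to 69 events by 54 centres would leave most strata with one event or none.
- That the prognostic data are wasted. Age, creatinine and diabetes are used for subgroups; of the four factors considered here, only heart failure has no stated use in the analysis.

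**Conclusion.** The point holds as a modest efficiency improvement for the primary outcome only. The crude chi-square is valid and gives about 90% power at 2,300 patients. Under an assumed centre SD of 0 to 0.8 logits it overstates the SE by 0 to about 4%, has a type I error between 5% and about 4.2%, and loses 0 to about 1 point of power. Adjusting for baseline risk factors would add about 0.3 to 3 points under an assumed AUC of 0.58 to 0.75. Direction is secure; size rests on those two assumed ranges. The 30-day log-rank and Cox analyses need no change on this ground.

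**What to change.** In Statistical Analysis Plan, before database lock:

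- Make the primary test a Cochran-Mantel-Haenszel test stratified by centre, with the Mantel-Haenszel risk ratio and its 95% confidence interval.
- Add a prespecified covariate-adjusted risk ratio from a logistic model with standardization, using baseline creatinine, age, diabetes and heart failure.
- Keep the crude chi-square as a sensitivity analysis.
- Leave the log-rank test and Cox models unstratified.

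The cost is wording: no new data, no change to the sample size. The article reports 810 of 2,300 patients randomized, and Blinding bars any analysis by study group until the database is locked, so the change can still be prespecified. Made after lock, it would be post hoc.

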### Interventions

#### Study Drugs

The study drugs (acetylcysteine 1200 mg or matching placebo) will be administered orally twice daily for two doses before the procedure and two doses after the procedure (Figure 1). On occasion, when the patient is included in the study on the same day of the angiography, the pragmatic design of the ACT trial allows one dose to be administered at least 6 hours before the procedure and three doses after it.

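### The subgroup rule infers an effect from any of five homogeneity tests at an unadjusted 5% level, and one of the five splits, contrast volume, is not a baseline factor

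*Protocol article*

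**What the plan says.** The Statistical Analysis Plan section sets the level in the paragraph on the primary endpoint: "Statistical significance will be inferred using a significance level of 0.05". Two paragraphs later it gives the rule for subgroups: "A subgroup effect will be inferred when the chi-squared test for homogeneity of effects is statistically significant". Five splits of the primary outcome follow: age at 70 years, sex, previous renal failure, diabetes, and "Amount of contrast agent <140 mL vs. ≥140 mL". All five fall under the same rule. No separate level, ordering or exploratory label is attached to them.

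The timing of the fifth factor follows from other sections. Randomization and Allocation Concealment says "Patients are randomized after providing a written informed consent in a 1:1 ratio to receive acetylcysteine or matching placebo". Study Drugs says the drug is "administered orally twice daily for two doses before the procedure and two doses after the procedure", with a same-day option of one dose at least 6 hours beforehand. The caption of Figure 1 places angiography no earlier than 6 hours after the first dose. The contrast item ("Contrast: type, volume administered") is listed under Treatment Data, not Baseline Data.

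**The concern.** Two things are fixed badly.

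- **The rule.** It turns each significant homogeneity test into a stated conclusion. With five such tests at 5%, a trial with no true heterogeneity has a sizeable chance of reporting a subgroup effect. The Background names the question of which population benefits most as unresolved, and the Discussion expects the results to matter for practice, so a subgroup claim from this trial would attract attention.
- **The fifth factor.** Age, sex, renal function and diabetes are known before randomization. Contrast volume is not: it is determined at the procedure. Listing it with the other four under one inference rule invites the reader to treat it as a characteristic that identifies in advance who benefits.

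**Working it through.** **Inputs.** From Sample size: control risk 15%, relative risk reduction 30% (so 10.5% on acetylcysteine), 90% power, two-sided 5%, N = 2,300. Allocation is 1:1, so 1,150 per arm. From the Statistical Analysis Plan section: five tests, level 0.05. From Table 1 (first 810 patients): 57% over 70, 38% female, 18% with creatinine above 1.5 mg/dL, 57% diabetic. Assumed, because the article does not give it: half the patients on each side of 140 mL.

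**1. The plan's own figure.** The article gives no error rate for the subgroup tests, so the sample size is the figure to reproduce. Per arm, (1.960 + 1.282)² × (0.15×0.85 + 0.105×0.895) / 0.045² rounds up to 1,150, total 2,300. The pooled-variance form gives 1,153 per arm, total 2,306. Power at 1,150 per arm is 89.9%. The stated size holds.

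**2. Chance of at least one false subgroup claim under homogeneous effects.**
- Independent tests: 1 − 0.95⁵ = 22.6%.
- Upper bound under any dependence: 5 × 0.05 = 25%.
- The five tests share the same patients, so this was simulated (five log risk ratio homogeneity tests, 2,300 patients, 4,000 runs per setting). With no effect and with a uniform risk ratio of 0.7, and with and without the negative age–diabetes association that the entry criteria would tend to create, the rate was 21.9% to 23.0%.
- Dropping only the contrast split leaves 1 − 0.95⁴ = 18.5%, so removing it does not by itself cure the multiplicity.
- At 0.01 per test: 1 − 0.99⁵ = 4.9%.

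**3. Power for a real interaction in an even split.** Take a risk ratio of 0.7 in one half and 1.0 in the other, 575 per arm in each half, control risk 15% in both (assumption).
- Variance of the log risk ratio where it is 0.7: 0.85/86.25 + 0.895/60.375 = 0.0247. Where it is 1.0: 2 × 0.85/86.25 = 0.0197.
- SE of the difference: √(0.0247 + 0.0197) = 0.211. |ln 0.7| / 0.211 = 0.357/0.211 = 1.69.
- Power at 0.05: Φ(1.69 − 1.96) = 39%. At 0.01: Φ(1.69 − 2.576) = 19%.
- Using the larger variance in both halves: SE = √(2 × 0.0247) = 0.222, power 36% at 0.05 and 17% at 0.01.

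**4. Timing of the five factors.**

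| Factor | Where recorded | Known at randomization? |
|---|---|---|
| Age, sex | Baseline Data | Yes |
| Renal failure, diabetes | Baseline Data (creatinine, inclusion criteria) | Yes |
| Contrast volume | Treatment Data | No: after randomization and at least one dose |

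**The case against.** The strongest reply is that this is mostly an omission. A journal article condenses the plan, the subgroup sentence itself names no level, and a separate analysis plan could add an adjustment or an exploratory label. The sentence may be meant only to require an interaction test instead of separate within-subgroup p-values. The list is also short, pre-specified and confined to one outcome. Part of this stands: the choice of test and the short list are sound, and carrying 0.05 over from the primary-endpoint paragraph is a reading, though the natural one because no other level appears. But the article does more than stay silent. It says what will be concluded from a significant test, and an analysis that followed it as written would have the error rate shown.

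Some stronger readings are tempting, and the documents do not support them:

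- **That the contrast split is materially biased.** Patients and staff are blinded, and nothing in the article suggests that one or two masked oral doses would change the volume of contrast used. A post-randomization factor that treatment does not affect still leaves comparable arms within each stratum. Any bias is probably small.
- **That the split breaches intention-to-treat because patients whose angiography is cancelled have no contrast volume.** The Outcomes section defines the primary outcome relative to angiography, so such patients have no defined primary outcome either. The split loses nobody on that ground whom the primary analysis could count.
- **That the subgroups are confirmatory.** The article never calls them so and allots them no alpha or sample size.
- **That 23% is the share of subgroup claims that would be false.** It is the chance of at least one claim when no heterogeneity exists. The false share depends on how plausible true interactions are, which the article does not state.

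**Conclusion.** The point holds as a matter of how subgroup results will be interpreted. Followed as written, the rule carries about a 22 to 23% chance of at least one false subgroup claim under homogeneous effects, bounded at 25%. This rests on applying 0.05 to each homogeneity test; the near-independence of the five tests is supported by simulation. The contrast-volume split is not a baseline subgroup, and a significant result there cannot be presented as baseline effect modification, even though blinding keeps the likely bias small.

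A reader might infer that a Bonferroni correction is required. It is not, if the analyses are labelled exploratory. A strict level has a real price: it roughly halves interaction power that is already low. The primary comparison, its error rate and the sample size are untouched.

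**What to change.** In the Statistical Analysis Plan section:

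1. Replace the inference rule with a statement that subgroup analyses are exploratory and hypothesis-generating, with the homogeneity test reported as a guide to interpretation.
2. Commit to reporting all five interaction tests, with estimates and confidence intervals, and say plainly that five were done.
3. Take contrast volume out of the list of baseline subgroups and present it separately as a descriptive analysis by a post-randomization variable.
4. Only if the sponsor wishes to keep an inferential subgroup claim, state a multiplicity-adjusted level. For five tests, 0.01 each gives a familywise rate of about 4.9%.

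Steps 1 to 3 change wording only. They need no new data and no change in conduct, and should be settled before the database is locked. Step 4 lowers power for a risk ratio of 0.7 versus 1.0 in an even split from roughly 36–39% to about 17–19%, which is a reason to prefer the exploratory label.

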### Ethical Aspects

Each study site will submit the study protocol to its institutional Research Ethics Board (REB). The study should start only after being approved by the REB. Written informed consent will be obtained from all participants. This study is in compliance with the Helsinki Declaration.

### Trial Organization and Management

#### Trial Management Team (TMT)

A team based on the Research Institute -Hcor, São Paulo, Brazil, will manage the trial on a day-to-day basis. The TMT is comprised by the chief investigator, a project manager, a clinical research associate, a statistician and four computer programmers. Data management is assumed by both the medical project manager and the clinical research associate.

The responsibilities of the TMT include:

- Selecting and training participant centers;

- Assisting trial centers with regulatory submissions;

- Distributing and supplying study sites with the study drug and forms;

- Monitoring recruitment and follow-up at participant centers;

- Data management: Elaboration, testing and maintenance of the electronic data capture system; data quality control;

- Data analysis;

- Servicing the Trial Steering Committee.

#### Trial Steering Committee (TSC)

The TSC is responsible for providing overall supervision of the trial, assist with development of the study protocol and preparing the final manuscript. All other trial's committees report to the TSC. The TSC members are epidemiologists, with in-dept training in designing and conducting randomized controlled trials, or cardiologists experienced in the conduction of multicentre clinical trials.

#### Trial Centers

Fifty four invasive catheterization centers in Brazil are participating in the study. Details of the participating centers are given in the Appendix.

#### Publication policy

The ACT study success depends on all its collaborators. Therefore, the primary results of the trial will be published under the name of ACT Trial Investigators. The contributions of all collaborators, their names and respective institutions, not only the members from TSC or TMT, will be acknowledged in the manuscript. To safeguard the scientific integrity of the study, data from this study will be submitted to publication only after the final approval from the TSC.

